**RESEARCH PROJECT**

**3 – INTRODUCTION**

Tooth whitening is considered a conservative treatment to remove pigments that promote unwanted darkening of the teeth, 1,2,3 and it is recommended to treat patients who seek improvements in dental appearance, as it presents a minimally invasive approach when compared to other treatments. invasive aesthetics. 4 Carbamide peroxide (PC) is one of the active components used in the whitening gel, which is available in different concentrations.1,5 The oxidizing agent present in PC is capable of diffusing through dental enamel and dissociating into unstable free radicals. (perhydroxyl, hydroxyl and oxygen) which react with the macromolecules of organic pigments, triggering the breakage of the pigments' carbon double bonds, resulting in smaller molecules that provide a change in the absorption spectrum, leaving the tooth lighter. 5

A very common unwanted effect during home bleaching treatment is tooth sensitivity.6,7,8,9 This sensitivity is reported to occur, generally, in the first weeks of treatment.10,11 This sensitivity is related to the amount of free radicals. free of carbamide peroxide that reach the pulp through the dentinal tubules.12,2,13,14 To reduce the pain caused by the bleaching treatment, some methods can be used, such as the use of gels with lower concentration and/or reduction of time. , frequency of application of the whitening gel,12,2 administration of analgesics/anti-inflammatory drugs15 and the use of desensitizers.5,9,16,3

Many agents with different mechanisms of action have been described and evaluated in the literature related to the management of HD. Dentin desensitizers can be classified, according to their action, as neural ones (e.g. potassium nitrate and low power lasers), which act on nerve cell stimulation, more specifically the Na + / K + pump in the membrane cell membrane, interfering with cell membrane polarity, increasing membrane action potential amplitude, and blocking the transmission of painful stimuli, 17 dentinal tubule blockers, for example, oxalates, glutaraldehyde and high-power lasers, in which they generate precipitates capable of occluding open dentinal tubules below the surface, interfering with the hydrodynamics of the dentinal fluid, thus preventing dentin sensitivity,18 and agents with both actions (e.g. potassium oxalate), in which oxalate has the action of forming insoluble precipitates in the dentinal tubules blocking the movement of dental fluid, and potassium that acts to reduce the transmission of nerve impulses .19

Among desensitizers, potassium oxalate has been widely used in clinical practice, with satisfactory results, without side effects.20,21,22 The mechanism of action of this agent is based on the obliteration of exposed dentin tubules, due to precipitation of crystals. oxalate 23 and depolarization of nerve endings.17 In a systematic review of the literature, in which the effectiveness of different desensitizing agents in reducing dentin sensitivity was evaluated, it was observed, based on the results of the authors, 24 that oxalate potassium had a significant effect on pain reduction. To date, there are no reports in the literature of clinical studies that evaluated the effect of 1.5% potassium oxalate in the control of sensitivity after home bleaching with 22% carbamide peroxide, justifying the objectives of this scientific investigation.

Tooth color is considered a phenomenon of great complexity influenced by factors such as ambient lighting conditions, translucency, opacity, light scattering, brightness and also by the structures and morphophysiological processes of vision that vary in each individual.25 Color perception it is subjective and needs more quantitative support to be evaluated. The spectrophotometer is an equipment capable of measuring the wavelength of a given radiation from the reflectance or transmittance of an object.26 In this study, we will use the EasyshadeAdvanced spectrophotometer (Vita-Zahnfabrik, Germany), using the CIE L*a system *b*, to assess color change between groups bleached with 22% carbamide peroxide. It is worth mentioning that the CIEL*a*b* color system is capable of converting the human eye's response to colors, so that it is electronically measured. 26

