**6 – METHODOLOGY**

## **6.1. Ethical aspects**

## This research project will follow the recommendations of the “consort” (consolidated standards of reporting trials). The research volunteers will be duly clarified and informed about the risks, methods and objectives of this project, being necessary the signature of the free and informed consent term – tcle (Annex I), in accordance with the Helsinki Declaration.41

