## **6.2. Sample selection**

Fifty volunteers aged between 18 and 29 will be selected, who must follow the inclusion and exclusion criteria described in table 1. The clinical evaluation of the volunteers will be carried out through anamnesis, intraoral clinical examination and color registration. All participants will undergo prophylaxis performed with a rubber cup (Microdon, SP, Brazil) and pumice stone (Biodinamic, PR, Brazil) seven days before the start of the study and will receive oral hygiene kits, to be used throughout the treatment, for the standardization of a toothpaste that does not have a desensitizing action and that does not contain fluor, in order to mitigate possible interferences in the evaluation of this study. The kit will consist of a toothbrush (Oral B, Cerdas Indicator, São Paulo, SP, Brazil) and a toothpaste (My First Colgate®, Colgate-Palmolive Company, SP, Brazil), under instructions for use three times a day.

Table 1: Inclusion and exclusion criteria.

| ***INCLUSION CRITERIA*** | ***EXCLUSION CRITERIA*** |
| --- | --- |
| - Shade greater than A2 in upper incisors and canines, according to the Vita Classical shade guide; - Absence of active caries lesions; - Patients who have never undergone bleaching therapy - Present good oral hygiene; - Not presenting hypersensitivity to tactile and evaporative stimuli through the Visual Analog Pain Scale; - Not being a smoker; - Not being pregnant; | - Patients undergoing fixed orthodontic treatment; - Non-vital teeth with darkening; - Presence of cracks or fractures; - Patients allergic to the product; - Extensive restorations in molars; - Presence of gastroesophageal dysfunctions; - Presence of dentinal exposure in anterior and/or posterior teeth; - Patients over 30 years of age. |

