**Analysis**

**Figure 1: Study design**

All groups will undergo home bleaching treatment with 22% Polanight carbamide peroxide (SDI). Only the G2 group will receive desensitizing treatment with 1.5% potassium oxalate gel (Table 2). Volunteers will be instructed on the use of whitening treatment and treatment with placebo or desensitizing.

**Table 2.** Division of groups, bleaching treatment, desensitizing treatments.

| ***GROUPS (N=50)*** | ***BLEACHING TREATMENT*** | ***DESENSITIZING TREATMENT*** |
| --- | --- | --- |
| **G1** |  | ---- |
| **G2** | Pola Night CP 22%  (SDI) | 1.5% Potassium Oxalate (Painless, BM4,SC, Brazil) |

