**6.6 Intervention**

Each volunteer in the group will receive a kit containing a tube with Polanight bleaching agent (SDI, SP, Brazil), two individual trays of ethylene/vinyl acetate copolymer (upper and lower), an unmarked tube with the desensitizer (potassium oxalate at 1.5%), a toothbrush and a fluoride-free toothpaste (My First Colgate®, Colgate-Palmolive Company, SP, Brazil).

*-Dental whitening*

The volunteers will be molded with alginate (Jeltrate Plus - Dentsply) with the aid of a tray (Tecnodent). Then, the models will be made using special plaster (Durone-Dentsply). The trays will be made from the models obtained using an ethylene/vinyl acetate copolymer (FGM) plate and a vacuum plasticizer (Plastivac P7/Bio Art). It will be recommended to apply a drop of the whitening agent Polanight (SDI, SP, Brazil) on each corresponding tooth in the tray that should be used for 45 minutes a day for a period of twenty one days.

- *Placebo*

After the bleaching treatment, the trays will be washed with running water, and the volunteers in group 1 will apply a small amount of the placebo gel, without active ingredient, with a color, texture and odor similar to 1.5% oxalate gel (Painless, BM4, SC, Brazil) in the spaces related to the buccal portions of the teeth of the trays, which should be used for 10 minutes. After removing the tray, the patient should brush the teeth with the fluoride-free toothpaste (My First Colgate®, Colgate-Palmolive Company, SP, Brazil).

*- Treatment with 1.5% Potassium Oxalate*

After the bleaching treatment, the trays will be washed with running water, and the volunteers in group 1 will apply a small amount of 1.5% oxalate gel (Painless, BM4, SC, Brazil) in the spaces related to the buccal portions of the teeth of the teeth trays, which should be used for 10 minutes. After removing the tray, the patient should brush their teeth with fluoride-free toothpaste (My First Colgate®) and clean the tray in order to remove all the gel inside the tray.

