## **6.11. Assessment of Oral Impact on Daily Performance (OIDP)**

## The OIDP will be used to measure the oral impact caused by bleaching treatment on individuals' ability to perform daily activities. It includes nine performances to be evaluated, based on the model by Masalu (2003),42 which analyzes physical, psychological and social activities, including eating, speaking and pronouncing correctly; teeth cleaning; sleep and relax; smiling, laughing and showing teeth without feeling ashamed and maintaining the emotional state without getting angry. For each reported impact, the patient will record the main symptom (1- tooth sensitivity, 2- tooth color, or 0- other reason). This questionnaire will be provided before and after the whitening treatment.

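### None of the four outcomes identifies a harm other than tooth sensitivity, so a sensitivity benefit would be reported with no other harm information by arm

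*Protocol*

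**What the plan says.** **Exposure.** Under Protocol section 6.6, the bleaching agent goes on each tooth "in the tray that should be used for 45 minutes a day for a period of twenty one days". The placebo or oxalate gel then goes into the rinsed tray, "which should be used for 10 minutes". Section 6.3 adds: "Volunteers will be instructed on the use of whitening treatment and treatment with placebo or desensitizing". The volunteers apply the products themselves.

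**Sample.** Section 6.2: "Fifty volunteers aged between 18 and 29 will be selected". Figure 1 divides them 25 and 25.

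**Risk.** Section 6.1 has volunteers "duly clarified and informed about the risks, methods and objectives of this project". Table 1 excludes "Patients allergic to the product". Section 3 names tooth sensitivity as a common unwanted effect of home bleaching and describes oxalate, citing earlier work, as used "potassium oxalate has been widely used in clinical practice, with satisfactory results, without side effects". The same section says that no clinical study has yet evaluated 1.5% oxalate after home bleaching with 22% carbamide peroxide.

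**Outcomes.** Section 5 sets four hypotheses: sensitivity, colour change, health-related quality of life and satisfaction. Sections 6.9 to 6.12 give the matching measurements. For each OIDP impact, the volunteer codes the main symptom as "1- tooth sensitivity, 2- tooth color, or 0- other reason". Section 6.13 names only the sensitivity values as data to be analysed.

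**The concern.** The trial asks whether adding a gel to home bleaching helps the volunteer. The answer needs the benefit on sensitivity and at least a description of anything else the gel, or the gel combined with peroxide, may do. The measurements supply the first and leave the second unrecorded.

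Two things follow. First, a reduction in sensitivity could be reported with nothing by arm on other harms, for a combination that the protocol itself describes as clinically unstudied. Second, the daily score covers discomfort as well as sensitivity. A sore gum may therefore raise the efficacy measure with no means of telling it apart from tooth pain.

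This is a question of data collection. An analysis plan, seen or unseen, can decide how to summarise what was recorded, but it cannot supply events that nobody wrote down.

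**Working it through.** **Step 1: is there a figure to reproduce?** No. The protocol states no harm rate, effect size or power.

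**Step 2: can each outcome identify a harm other than tooth sensitivity?** Gum or mucosal irritation and allergic reaction serve as examples. The protocol does not list them as expected events.

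| Outcome | What is recorded | When | Identifies another harm? |
|---|---|---|---|
| Colour (6.9) | Spectrophotometer reading of upper incisors and canines | Baseline and two later readings | No; no soft-tissue inspection |
| Sensitivity (6.10) | One number, 0-10, for sensitivity or discomfort caused by bleaching | Daily for 21 days | No; gum discomfort could raise the number without being named |
| OIDP (6.11) | Impact on daily activities, with three cause codes | Before and after treatment | No; everything except sensitivity and colour shares one code |
| Satisfaction (6.12) | Satisfaction and recommendation scales, five questions | End of treatment | No |

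Result: 0 of 4. The intraoral examination in section 6.2 serves selection. Section 6.1 lets volunteers leave at any time but does not provide for recording a reason.

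**Step 3: what could 25 volunteers per arm show if harms were recorded?** Input: n = 25 in the oxalate arm (Figure 1).

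Upper 95% limit when no event is seen:
- one-sided: 1 − 0.05^(1/25) = 0.113, or 11.3%
- two-sided (Clopper-Pearson): 1 − 0.025^(1/25) = 0.137, or 13.7%

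Chance of at least one event in 25, 1 − (1 − p)^25, for assumed true rates p that are not in the protocol:

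| Assumed p | Chance of at least one event |
|---|---|
| 1% | 22% |
| 2% | 40% |
| 5% | 72% |
| 10% | 93% |

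Power to detect a difference between arms (25 per arm, two-sided 5%, rates again assumed): 5% against 15% gives 21%; 10% against 30% gives 42%; 5% against 40% gives 87%.

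Recording would therefore probably reveal a harm that affects one volunteer in ten or twenty. It would not show that rarer harms are absent, and it would not support a formal comparison unless the difference were very large.

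**Step 4: when must harms be captured?** Section 6.9 times the later colour readings by reference to 21 days and to one month after the last gel application. On one reading of that sentence, both fall after treatment has ended. An inspection then could miss irritation that arose and settled during bleaching. The only instrument certain to cover the treatment days is the daily questionnaire.

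**The case against.** The strongest case against has four parts.

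- **Sensitivity is a harm, and it is measured.** This stands. It is the unwanted effect that section 3 names; it is scored daily in both arms and compared under H01. The point is therefore confined to harms other than sensitivity. That the score and the OIDP code might pick up another problem does not fill the gap, because neither says what the problem was.
- **The remark about side effects is background.** This also stands. A reader might infer that the trial is defective because it cannot support or refute that remark. The documents do not support this: the remark is a cited statement in the Introduction, outside the four hypotheses. Nor could the trial confirm it after the fix, since zero events in 25 leaves rates of up to 11-14% open.
- **Reporting routes may lie in pages not available here.** A reader might infer that a volunteer harmed at home has no way to tell the team. That cannot be shown, because the consent and contact pages were removed before review. It does not rescue the outcome sections: a list of risks or a telephone number is not a record of events by arm.
- **This is a request for an extra outcome, and no statement in the protocol is false.** That is fair as to weight. It is why the point is put as an inexpensive improvement. The sensitivity comparison can proceed without it.

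**Conclusion.** The point holds in this limited form: 0 of the 4 outcomes identifies a harm other than tooth sensitivity, and a benefit would be reported with no further harm information by arm. Its statistical reach is small. With 25 per arm the data would be descriptive, and the 11.3% and 13.7% limits describe what a repaired trial could say; they do not measure an error in the present plan.

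The conclusion assumes that the visible outcome sections are complete. That the products are used without supervision is inferred from home use. That the gel is applied on each of the 21 days is inferred from its placement after each bleaching session. The point does not depend on either inference.

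**What to change.** 1. **Daily questionnaire (6.10):** add one free-text line for any problem other than tooth sensitivity, including gum soreness, separate from the 0-10 score. This line carries the capture of events during the 21 treatment days and helps keep gum discomfort apart from the sensitivity measure.
2. **Colour visits already planned (6.9):** add a brief inspection of gums and oral mucosa and one open question about other problems. The baseline visit gives the comparison for the later two.
3. **Reporting (6.13):** tabulate events, and withdrawals related to them, by arm. Describe them only, and state the upper limit that goes with any zero count.

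Cost: a few minutes per visit, one diary line and one table. No extra visit is needed.

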**4 – JUSTIFICATION**

Oxalates, in particular, have a long history in the treatment of HD 27,28,29 and are widely recognized as capable of reducing postoperative sensitivity.30 Treatment with oxalate-based products is capable of decreasing dentin permeability. ,31,32,33 form precipitates in the dentin tubules,34 block fluid flow 35,36 and reduce HD-related pain.

Oxalate precipitates are also relatively insoluble in acid, making them resistant to dissolution in the oral environment.37 The combination of potassium and oxalates was introduced for DH in the late 1970s31 and produced two main effects: an initial effect, from potassium ions, characterized by neutral depolarization; and late effect, resulting from obstruction of the tubules by the formation of calcium oxalate crystals.38 The latter is based on the exchange of ions between the metal ions present in the oxalate (potassium) and those (Ca2+) in the dentinal fluid. The exchange of Ca2+ for K+ leads to the formation of a 'slightly soluble' calcium oxalate crystalline layer, which is deposited on the dentin surface.

The color system – CIE L*a*b*, which will be used in this study, is based on the theory of color perception of the three receptors in the eyes (three types of retinal cones) separated by the primary colors – red, green , blue.26 Through this system the reflectance spectrum is filtered so that the spectrum of the red, green and blue hue is extracted as three coordinates, and processed to give the answer L*a*b*.39 The letters of the acronym CIE L*a*b* relates to the three directions in the color sphere: L* stands for color luminosity, the chromatic coordinates a*(represent red–green) and b* (represent yellow–blue), are perpendicular to L* and they leave in four orthogonal directions (a+): characterizing the reddish color; (a-): characterizing the color green; (b+): characterizing a tendency to yellow; and (b-): with a color tendency towards blue hue.26,27

In addition to the a* and b* attributes, their combination also determines Chroma (C*) and H* (Hue) parameters.27 Chroma is the color saturation, it measures the distance from the L* axis in that system and represents the change of a opaque, duller state to a saturated, vivid color. Hue (H *) is an angle measure that determines the predominant wavelength that makes up that color (predominant hue). 39 Color can be determined by a combination of intrinsic and extrinsic staining effects, the first related to light scattering and the absorption properties of enamel and dentin, determined by their morphophysiological conditions, and the other associated with the absorption of pigments on the surface of the tooth. tooth enamel. 40

This randomized, placebo-controlled clinical study will therefore positively contribute to the elucidation of the effectiveness of 1.5% potassium oxalate in controlling pain sensitivity after home bleaching treatment, as well as in the perception of color change between the groups. bleached with 22% carbamide peroxide.

**RESEARCH PROJECT**

**5 – OBJECTIVE**

This randomized, placebo-controlled clinical trial aims to evaluate the effect of 1.5% potassium oxalate in controlling pain sensitivity and color change after at-home tooth whitening. The null hypotheses tested in the present study will be: H01 - There will be no difference in tooth sensitivity between the groups bleached with 22% carbamide peroxide associated or not with 1.5% potassium oxalate, thirty days after the end of treatments.

H02- There will be no difference in color change between the groups bleached with 22% carbamide peroxide associated or not with 15% potassium oxalate, thirty days after the end of treatments.

H03- Use of 1.5% potassium oxalate after bleaching treatment will not influence Health-Related Quality of Life (HRQoL).

H04- Use of potassium oxalate after bleaching treatment will not influence patient satisfaction.

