**G2 (n=25)**

Experimental Group

(1.5% Potassium Oxalate)

Pain assessment by daily questionnaire

(n=50)

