**6.9. Color Assessment**

Color evaluation will be performed on the upper incisors and canines of each volunteer with an EasyshadeAdvanced spectrophotometer (Vita-Zahnfabrik, Germany), using the CIE L*a*b* system, where the values ​​of color change (E) were obtained for each group of teeth using the formula: E = {(L)2 + (a)2 + (b)2}1/2 , where: L* = L*- L*0; a* = a*-a*0; and b* = b*- b*0. The color evaluation will be performed at three times: before the whitening treatment serving as a baseline, 21 days and 1 month after the last application of the whitening gel.

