## **6.10. Sensitivity assessment**

## Postoperative sensitivity will be evaluated through a daily questionnaire that will be provided to volunteers from the first at-home bleaching treatment session, which must be completed during the 21 days of treatment, according to their personal perception and pain threshold, on the level of sensitivity or discomfort caused by the bleaching treatment, on a scale from 0 (no pain) to 10 (severe pain), according to Visual Analogue Scale.

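### H01 is set thirty days after treatment, but sensitivity is scored only during the 21 treatment days, so the trial collects no data that can test it

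*Protocol*

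**What the plan says.** Section 5 of the Protocol lists four null hypotheses. The first, H01, is that tooth sensitivity will not differ between the groups bleached with 22% carbamide peroxide "associated or not with 1.5% potassium oxalate, thirty days after the end of treatments". H02, on colour change, is given the same thirty-day time point.

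Section 6.10 is the only section that defines how sensitivity is measured. It describes a 0-10 visual analogue questionnaire "provided to volunteers from the first at-home bleaching treatment session", "which must be completed during the 21 days of treatment". Section 6.6 sets bleaching at "45 minutes a day for a period of twenty one days", so the diary and the bleaching period coincide. The flow chart in section 6.3 shows the same single instrument: "Pain assessment by daily questionnaire".

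Section 6.9 schedules colour readings "before the whitening treatment serving as a baseline, 21 days and 1 month after the last application of the whitening gel". Only colour is measured at that late visit.

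On when the symptom is expected, section 3 says: "This sensitivity is reported to occur, generally, in the first weeks of treatment".

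**The concern.** A hypothesis needs an observation at the time it refers to. H01 names a time about a month after the diary closes, and nothing else in the Protocol yields a sensitivity score then. Controlling sensitivity is the first-named aim of the trial, so this is the question that readers will look to it to answer.

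Two outcomes are possible if the text stays as it is:

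- H01 is not tested at all.
- H01 is tested on something else taken from the diary. With 21 daily scores per person, the candidates include the mean, the peak, any single day, or the proportion reporting any pain. If that choice is made with the data in view, the 5% significance level in section 6.13 no longer describes the error rate of the reported result.

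There is a further difficulty with the time point itself. The Protocol's own rationale places bleaching sensitivity early in treatment. A comparison a month after bleaching stops would probably be made when there is little sensitivity left in either group to reduce, and a null result there would say little about whether the desensitizer works.

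**Working it through.** No power or sample-size figure is involved. The check sets the measurement schedule against the time point of each hypothesis.

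**Inputs**

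- Bleaching period: 21 days (section 6.6).
- Sensitivity diary: first session to the end of the 21 treatment days, once daily (section 6.10).
- H01 and H02 time point: 30 days after the end of treatments (section 5).
- Late colour reading: 1 month after the last gel application (section 6.9).
- Participants: 50, in two groups of 25 (section 6.3).

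**Timeline, counted from the first bleaching day**

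- Sensitivity readings: days 1 to 21.
- H01 time point: 21 + 30 = day 51.
- Gap between the last sensitivity reading and H01: 51 − 21 = 30 days.
- Readings at the H01 time point: 0 of 21 per participant.
- Planned diary values for the whole trial: 21 × 50 = 1,050, all before the H01 time point.

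The result does not depend on how the end of treatments is read. The desensitizer or placebo gel is applied after bleaching, so the end of treatments cannot come before day 21, and thirty days later is always outside the diary window.

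**Hypothesis against data**

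| Hypothesis | Stated time | Data scheduled at that time |
| --- | --- | --- |
| H01, sensitivity | about day 51 | none |
| H02, colour | about day 51 | spectrophotometer reading at 1 month |

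**Could another part of the Protocol supply the missing reading?**

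- Section 6.2, Table 1: a visual analogue check for hypersensitivity, but at screening and for eligibility only.
- Section 6.5: refers to an evaluator of pain sensitivity, but no evaluator-administered assessment or visit is described anywhere.
- Section 6.11, the daily-performance questionnaire: "This questionnaire will be provided before and after the whitening treatment". No thirty-day time is given, and tooth sensitivity enters only as a coded reason for a reported impact, not as a score.
- Section 6.13: analyses the values that volunteers report, which are the diary values.

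None of these gives a between-group sensitivity score at thirty days.

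**The case against.** The strongest reply is that this is a slip of wording and not a failed design. H01 and H02 end in the same phrase, which fits colour and may simply have been carried over to sensitivity. H02 contains another apparent slip, giving the oxalate concentration as 15% where the rest of the document has 1.5%. The operative sections (flow chart, diary, analysis) agree with one another, and the data for the natural question, sensitivity during bleaching, are collected. This is plausible and explains why the repair is cheap. It does not remove the fault: to read H01 as a treatment-period hypothesis, one must override a time point that it states explicitly.

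Other points deserve weight:

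- The Protocol ranks no hypothesis and names no primary endpoint. Treating H01 as the leading one rests on its being listed first and matching the first-named aim.
- The Protocol gives no figure for sensitivity at thirty days. That it would be low in both groups is an inference from section 3. Section 4 also describes a late effect of tubule obstruction, which gives some reason to look later.
- An unseen statistical analysis plan might fix a summary of the diary in advance. That would limit selective choice, but it could not create a day-51 reading, and it would be testing a different hypothesis from the one in the Protocol.
- The counts of readings describe the mismatch. They do not measure bias or loss of power.

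**Conclusion.** The concern holds. H01 as written cannot be tested with the data the Protocol schedules: 0 of 21 sensitivity readings per participant fall at its time point, and the last one precedes it by 30 days. This follows from the Protocol's own schedule and needs no outside assumption. H02 is not affected.

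Two parts of the argument are judgement. One is that H01 is the leading hypothesis. The other is that a thirty-day comparison would probably find little sensitivity in either group. The contradiction stands without them. It must be resolved before analysis, because otherwise the trial has no stated sensitivity hypothesis that its data can answer.

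**What to change.** - **Restate H01** as no difference between the groups in tooth sensitivity during the 21 days of bleaching. Keep the thirty-day time point for colour (H02).
- **Name one per-participant summary with it**, before any comparison by group is seen. The mean of the 21 daily scores is a reasonable example, with the maximum score as secondary. An area under the daily curve would serve much the same purpose. It is not identical to the mean, since the trapezoidal form gives the first and last days half weight and the two can diverge when diary days are missing, so the formula should be written down.
- **If a post-treatment statement is still wanted**, add one 0-10 sensitivity score at the one-month colour visit and list it as a secondary endpoint. It cannot be recovered for participants who have already passed that visit.
- **If the sponsor did intend thirty days for H01**, that added score becomes essential, and section 6.10 and the flow chart must show it.

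The cost is a change to the wording of H01 and, optionally, one question at a visit already planned. Sample size, treatment and visit schedule are unchanged.
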